### CHARACTERISTICS OF THE SUBJECT POPULATION (3-10)

#### 3. ACCRUAL

- A. What is the number of subjects that must complete the study and be evaluable in order to achieve the scientific objectives of the research?** [See Educational Guide – Biomedical Research \(PedsIRB\)](#)

40 NICU infants who are between 23 and 32 weeks gestational age must complete the study.

- B. What is the statistical or other justification for the number of subjects needed to complete the study?** [See Educational Guide – Biomedical Research \(PedsIRB\)](#)

Based on our previous study, NICU infants who received 400 IU/day of Vitamin D are expected to have a mean discharge serum 25(OH)D of 23.1 ng/ml (standard deviation=7.0). Conservatively, the 800 IU dose group is expected to have a mean discharge serum 25(OH)D of 30 ng/ml (SD=7.0) (SD estimated from our previous study data). Assuming a 0.05 level of significance, and a total drop-out rate of 10 percent; 40 NICU infants randomized to the two dose groups will provide 81 percent power to detect a difference between doses.

- C. What is the maximum number of subjects that will be consented at all sites under the oversight of the PedsIRB and what is the justification for this number?** [See Educational Guide – Biomedical Research \(PedsIRB\)](#)

A maximum of 40 infants who are between 23 and 32 weeks gestational age will be consented for the study.

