## METHODS AND PROCEDURES (11-15)

### 11. METHODS AND PROCEDURES APPLIED TO HUMAN SUBJECTS

- A. Does this protocol require tests to be performed for the purpose of determining subject eligibility which would not be *routinely* conducted as part of standard clinical care of the prospective subject?

☒ No

☐ Yes. Describe the tests to determine subject eligibility. [See Educational Guide – Biomedical Research \(PedsIRB\)](#)

- B. Indicate the study design by checking the appropriate boxes.

[See Educational Guide – Biomedical Research \(PedsIRB\)](#)

☐ Phase I

☐ Phase I/II

☐ Phase II

☐ Phase II/III

☐ Phase III

☐ Phase IV

☐ Other:

☐ Case-Control

☐ Cohort

☐ Cross-sectional

☐ Randomized, parallel group

☐ Randomized, cross-over

☐ Placebo-Controlled

☐ Single Blind

☒ Double Blind

☐ Triple Blind

- C. Describe sequentially all procedures, interventions and evaluations to be applied to subjects, including follow-up. [See Educational Guide – Biomedical Research \(PedsIRB\)](#)

Step 1: Recruitment and Informed Consent

Parents of infants admitted to the NICU who meet eligibility criteria will be approached by study personnel, information about the study will be given, and informed consent will be obtained.

Step 2: Collection of Baseline Data

A sample of cord blood drawn that is drawn at birth for other routine clinical use will be frozen and stored at -70 degrees for study analysis of 25(OH)D levels. Demographic information will be obtained, including gestational age, birth weight, length, circumference, race, ethnicity, and season of birth. This is routine NICU admission information that is not performed exclusively for research purposes.

Step 3: Randomization

Study pharmacist will be notified and eligible infants will be randomized to the 400 IU/day of 800 IU/day supplementation group. Vitamin D supplementation will begin when the infant reaches full enteral feedings. Both the investigators and the subjects will be blinded as to the treatment group.

Step 4: NICU Data Collection

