Blood samples will be drawn every 4 weeks, beginning 4 weeks after birth. The maximum amount of blood taken at each blood draw will be 2 mL. The final blood draw will occur at 36 weeks CGA. Analysis of each blood sample will include 25(OH)D levels, PHT levels, and VDBP. A serum calcium will be obtained with each blood draw for safety monitoring purposes, if not already available from routine NICU lab monitoring. Lab draws in the NICU are done by the nursing staff and are done using heelstick or venipuncture, at the discretion of the nursing staff. Nurses may make more than one

attempt to draw blood, but if the lab draw cannot be successfully completed, the attempt is terminated at the discretion of the bedside nurse. Ongoing clinical data collection from the patients' medical record will include daily vitamin D intake, growth parameters, and infections/antibiotic use.

Step 5: Urine collection and DEXA Scan: When the infant reaches 36 weeks gestational age, a 24-hour urine sample will be obtained for measurement of calcium excretion. At 40-44 weeks gestational age, a DEXA scan will be performed.

| Test                                  | Frequency of Collection                                                                     | Amount of Blood                                                                                                                                                                                                                                                                    |
|---------------------------------------|---------------------------------------------------------------------------------------------|------------------------------------------------------------------------------------------------------------------------------------------------------------------------------------------------------------------------------------------------------------------------------------|
| 25(OH)D(ng/mL)                        | Collected on cord blood, every 4 weeks, and at 36 weeks CGA                                 | Requires < 0.5 mL                                                                                                                                                                                                                                                                  |

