The primary endpoint for statistical analysis is serum 25(OH)D level at discharge. Analysis will be done using intent-to-treat strategy, where infants will be included in the group to which they were assigned regardless of compliance. The statistical analyses will be done with SAS software. P-values less than 0.05 will be considered statistically significant. Baseline characteristics (e.g. gender, season of birth) will be compared between the dose groups, stratified by race and gestational age, to ensure comparability of the groups using Mann-Whitney tests for continuous variables and Fisher's exact tests for categorical variables. Analysis of covariance (ANCOVA) will be conducted to test for differences in discharge serum 25(OH)D level between the dose groups while adjusting for known confounders (race, gestational age, gender and season of birth). If the overall F-tests are significant then pairwise comparisons will be made and p-values for these comparisons will be adjusted for multiple comparisons using Tukey's method. Correlation methods will be used to look at associations between 25(OH)D levels and iPTH levels at discharge. Descriptive plots will be used to evaluate changes in serum 25(OH)D levels. DEXA scan results evaluating total body minus head bone mineral density (BMD) will be compared between the two groups. Descriptive plots will be used to evaluate changes in serum 25(OH)D levels. All tests will be 2-sided and p-values <0.05 will be considered statistically significant.

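### The primary ANCOVA omits cord-blood 25(OH)D, the baseline of its own endpoint; validity is unaffected, but precision may be lost, by an amount the protocol does not let one fix

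*Protocol*

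**What the plan says.** Section 11.E of the protocol states: "The primary endpoint for statistical analysis is serum 25(OH)D level at discharge". The dose groups are compared by ANCOVA "while adjusting for known confounders (race, gestational age, gender and season of birth"; no further covariate is named. Change in 25(OH)D is otherwise only plotted.

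The baseline value is in the plan. Under section 11.C, Step 2 (baseline data), cord blood "will be frozen and stored at -70 degrees for study analysis of 25(OH)D levels", and randomization follows in Step 3. The sampling table lists 25(OH)D as "Collected on cord blood, every 4 weeks, and at 36 weeks CGA". No model in the protocol uses the cord value.

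The sample size in section 3.B assumes for the 400 IU arm a "mean discharge serum 25(OH)D of 23.1 ng/ml (standard deviation=7.0"), and for the 800 IU arm a "mean discharge serum 25(OH)D of 30 ng/ml (SD=7.0").

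**The concern.** A baseline measurement of the endpoint is usually the first candidate for an ANCOVA covariate. The protocol's own background points the same way: it describes the newborn as wholly dependent on maternal vitamin D and born at about 80% of the mother's level. Race and season of birth are indirect markers of that supply; cord 25(OH)D measures it. Gestational age does not stand in for it either: in the investigators' previous study its correlation with cord 25(OH)D was 0.35, so it explained about 0.35² = 12% of the cord variance.

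With few infants, chance differences in starting level can be sizeable. Taking the previous study's cord SD of 7.0 and 18 infants per arm, the standard error of the between-arm difference in mean cord level is 7.0 × √(2/18) = 2.33 ng/mL, so differences up to 1.96 × 2.33 = 4.6 ng/mL fall in the 95% range. What passes into the dose estimate is that difference times the cord-to-final slope, less what the listed covariates already absorb. Whatever cord 25(OH)D could explain beyond those covariates stays in the error term. Section 3.C caps consent at 40 infants, so recruitment cannot make up lost precision.

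**Working it through.** **Inputs.** Difference 30 − 23.1 = 6.9 ng/mL, SD 7.0, 40 infants and 10% drop-out (section 3.B); level 0.05 (section 3.B: "Assuming a 0.05 level of significance"), two-sided (section 11.E: "All tests will be 2-sided and p-values <0.05 will be considered statistically significant"). Assumed, because not stated: 1:1 allocation; six covariate degrees of freedom for the planned model (gestational age 1, gender 1, race 1, season 3); residual SD 7.0 after those covariates; and r, the partial correlation of cord with final 25(OH)D given them.

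**Step 1: the plan's own figure.** 40 × 0.9 = 36 infants, 18 per arm. SE = 7.0 × √(2/18) = 2.333; noncentrality 6.9/2.333 = 2.957; 34 df; critical t 2.032. Power is 81.9%, which agrees with the stated 81%. This is a two-sample t-test with no covariates.

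**Step 2: the planned ANCOVA.** With k covariate df and N = 36, chance imbalance in the covariates inflates the variance of the dose effect by 1 + k/(N − 3 − k) on average. For k = 6 this is 1 + 6/27 = 1.222. SE = 2.333 × √1.222 = 2.580; noncentrality 2.675; 28 df; power 73.3%. Averaging power over the distribution of the imbalance (R² of arm on covariates taken as Beta(k/2, (35 − k)/2)), rather than inserting its mean effect, gives about 74%.

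**Step 3: add cord 25(OH)D.** Residual SD = 7.0 × √(1 − r²). One more df gives k = 7 and inflation 1 + 7/26 = 1.269; with a missing-sample indicator as well, k = 8 and inflation 1 + 8/25 = 1.320. Power averaged over imbalance:

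| Model | r | Residual SD | Cord only added | Cord plus indicator |
|---|---|---|---|---|
| Planned | n/a | 7.00 | 74% (not added) | n/a |
| With cord | 0.2 | 6.86 | 74% | 72% |
| With cord | 0.3 | 6.68 | 76% | 74% |
| With cord | 0.4 | 6.42 | 79% | 77% |
| With cord | 0.5 | 6.06 | 83% | 82% |

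Inserting the mean inflation instead gives 73.3%, 75.6%, 78.8% and 83.2% for cord only, within half a point. Worked line for r = 0.5: SE = 6.06 × √(2/18 × 1.269) = 2.277; noncentrality 6.9/2.277 = 3.03; 27 df; 83.2%.

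**Step 4: break-even.** The addition narrows the standard error when (1 − r²) × 1.269 < 1.222, that is r² > 0.037, or r > 0.19. With the indicator, (1 − r²) × 1.320 < 1.222 gives r² > 0.074, or r > 0.27. The lost degrees of freedom push both up slightly, to about 0.2 and 0.3.

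**The case against.** **The listed covariates may already take much of the gain.** If race, season and gestational age are markers of maternal supply, cord 25(OH)D adds only what they miss. This stands, and it is why the comparison is between the planned ANCOVA and the same model plus cord 25(OH)D. A reader might instead compare cord 25(OH)D as the only covariate with no covariates at all. That gives 85.3%, 91.2% and 98.0% power at correlations of 0.3, 0.5 and 0.7 against 81.9%, or at 0.5 an apparent 36/(1 − 0.25) = 48 infants for the price of 36. The protocol plans neither model, so those figures overstate the increment.

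**The correlation may be weak.** No figure for it is given. Infants are born at 23 to 32 weeks and the last scheduled draw is at 36 weeks CGA, so roughly 4 to 13 weeks separate the two values. Supplementation starts only at full enteral feeding, so the cord value is the level at birth and not at the start of treatment. This stands too: at r near 0.2 the gain is nil, below that there is a small loss, and a value as high as 0.7 has no support in the document.

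**Not every infant need have a sample.** A reader might infer universal baseline data. The sample is left over from routine cord blood (sections 11.C and 18.A), and section 8 does not make one a condition of entry. A missing-data rule is therefore needed and may cost a second degree of freedom.

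**Nothing is invalid.** A reader might infer bias from the omission. Randomization protects the comparison, the standard error covers chance imbalance, and the stated 81% does not rely on baseline adjustment. This is right: the point concerns efficiency alone.

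Against this, the protocol fixes the covariate list itself, so the choice is open to comment without sight of a separate analysis plan.

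**Conclusion.** The point holds as a possible loss of precision. The planned ANCOVA leaves out a pre-randomization measurement of its own endpoint that the trial already intends to assay. Under the stated assumptions, adding it moves power from about 74% to 74%, 76%, 79% or 83% as the partial correlation goes from 0.2 to 0.5, less 1 to 2 points where a missing indicator is fitted. The true gain cannot be read from the protocol.

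The 74% should not be taken as a correction of the stated 81%. It assumes that the SD after covariate adjustment is still 7.0. The protocol takes 7.0 from the previous study and does not say how much of it the listed covariates explain; if they explain some, power is higher with or without cord 25(OH)D. The coding of race and season is also assumed: with four covariate df in place of six, the same calculation gives about 77% without cord 25(OH)D and 86% with it at r = 0.5; with seven, about 72% and 82%. The break-even stays near 0.2 in each case.

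**What to change.** In section 11.E, add cord-blood 25(OH)D as a prespecified continuous covariate in the primary ANCOVA. State the rule for infants without a usable cord sample: impute the pooled mean of the observed cord values, and add a missing indicator if any are missing, so that no randomized infant leaves the intent-to-treat analysis on this account.

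Before fixing the model, the investigators could estimate the partial correlation from their previous study, which reports both cord and discharge 25(OH)D. Those infants were above 32 weeks gestation, so the estimate would be a guide only.

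The cost is a sentence or two in 11.E and one or two degrees of freedom, with no added sample or assay. The downside is a small loss of power if the partial correlation is below about 0.2, or below about 0.3 when the indicator is needed. Settling this now also avoids a later, data-driven decision to adjust if cord levels turn out imbalanced.

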**F. Does this research involve genetic testing?**

☒ **No**

☐ **Yes. Attach [Addendum G](#).** [See Educational Guide – Biomedical Research \(PedsIRB\)](#)

**G. After completion of this research, will any un-used HBM be used to create a tissue bank for future research?** [See Educational Guide – Biomedical Research \(PedsIRB\)](#)

☒ **No.**

☐ **Yes. Respond to the following:**

- 1) **What is the location of the tissue bank?**
- 2) **Where will the HBM be stored and how will it be secured?**
- 3) **Who will have access to the HBM and what is the process for obtaining samples from the bank?**
- 4) **How will confidentiality be protected when HBM is released from the tissue bank?**
- 5) **What records will be kept regarding disposition of samples?**
- 6) **What is the procedure for a subject to withdraw his/her HBM?**
- 7) **Will any clinical data be obtained and banked with the HBM?**
  - ☐ **No**
  - ☐ **Yes. Respond to the following:**
    - a) **Specify the source of the clinical data (e.g., medical records).**

b) Specify what clinical data will be collected.

c) Indicate the HBM donor identifiers that will be recorded from the medical, or other record, and maintained (at any time) in association with the HBM. [See Educational Guide – Biomedical Research \(PedsIRB\)](#)

- ☐ Names
- ☐ Postal address information: street address, city, county, precinct, ZIP code
- ☐ All elements of dates (except year) related to an individual (e.g. birth, admission, discharge).
- ☐ Telephone numbers
- ☐ Fax numbers.
- ☐ Electronic mail addresses
- ☐ Social Security numbers
- ☐ Medical Record numbers
- ☐ Health plan beneficiary numbers
- ☒ Account numbers
- ☐ Certificate/license numbers
- ☐ Vehicle identifiers and serial numbers, including license plate numbers
- ☐ Device identifiers and serial numbers
- ☐ Web Universal Resource Locators (URLs)
- ☐ Internet Protocol (IP) address numbers
- ☐ Biometric identifiers, including finger and voice prints
- ☐ Full face photographic images [and any comparable images]
- ☐ Any other unique identifying number, characteristic, or code

OR

- ☐ No HBM donor identifiers will be recorded and maintained in association with the HBM.

## 12. DRUGS AND BIOLOGICS

A. Does this study involve an investigational drug or biologic?

☒ No

☐ Yes. Respond to the following:

1) Identify the investigational drug or biologic.

2) Provide the IND number and holder of the IND. If the IND is held by the PI, provide a copy of the FDA notification letter, or other verification and copies of the signed investigator statements (Form FDA 1572) for all required study personnel in accordance with 21 CFR 312.53. [See Educational Guide – Biomedical Research \(PedsIRB\)](#)

3) Describe the controls for securely storing and dispensing the investigational drug or biologic in both the in-patient and out-patient setting. [See Educational Guide – Biomedical Research \(PedsIRB\)](#)

B. Does this study involve the investigational use of an FDA-approved and marketed

drug or biologic? [See Educational Guide – Biomedical Research \(PedsIRB\)](#)

☐ No

☒ Yes. Respond to the following:

1) Does the drug or biologic have an IND number?

☒ No

☐ Yes. Provide the IND number and identify the holder.

2) Will the results of this study be used by the manufacturer to support (a) a new indication for the drug or biologic, (b) a significant change in the labeling for the drug or biologic, or (c) a significant change in the advertising for the drug or biologic?

☒ No

☐ Yes. Explain. [See Educational Guide – Biomedical Research \(PedsIRB\)](#)

3) Does the study involve a route of administration or dosage level, or use in a subject population or other factor that significantly increases the risks (or decreases the acceptability of the risks) associated with the use of the drug or biologic?

☒ No

☐ Yes. Explain. [See Educational Guide – Biomedical Research \(PedsIRB\)](#)

#### 13. FDA USE-IN-PREGNANCY CATEGORY

Provide an FDA Use-in-Pregnancy category (A, B, C, D or X) for each drug used as a part of this research. [See Educational Guide – Biomedical Research \(PedsIRB\)](#)

This study will administer Vitamin D3 to infants. Vitamin D3 is pregnancy category C. This recommendation is based on animal studies which have shown fetal abnormalities in several species associated with hypervitaminosis D similar to supravalvular aortic stenosis syndrome described in infants. Hollis et al have done several studies with high dose vitamin D in both infants and pregnant women without adverse events.

#### 14. DEVICES

A. Does this study involve an investigational device?

☒ No

☐ Yes. Respond to the following:

1) Identify and describe the investigational device.

2) Indicate the sponsor's determination of whether the device is significant risk (SR) or non-significant risk (NSR).

3) Provide the IDE number and identify the holder of the IDE for SR devices. If the IDE is held by the PI provide a copy of the FDA notification letter or other verification. [See Educational Guide – Biomedical Research \(PedsIRB\)](#)

4) Describe controls for securely storing and dispensing the device. [See Educational Guide – Biomedical Research \(PedsIRB\)](#)

- 5) Describe oversight procedures in place for departments, sections, or operating rooms where devices are used which provide for independent monitoring of the storage and dispensing of devices as well as required record-keeping. [See Educational Guide – Biomedical Research \(PedsIRB\)](#)

**B. Does this study involve the investigational use of an FDA-approved, marketed device?**

☒ **No**

☐ **Yes. Does the device have an IDE number?**

☐ **No**

☐ **Yes. Provide the IDE number and identify the holder.** [See Educational Guide – Biomedical Research \(PedsIRB\)](#)

**15. Confidentiality and Privacy**

**A. Where will research data be stored and how will it be secured?** [See Educational Guide – Biomedical Research \(PedsIRB\)](#)

Electronic data will be protected in accordance with UNMC Computer Use and Electronic Information Security Policy No 6051. All electronic devices are located in locked offices and are password locked and encrypted. Data will be entered and stored on the UNMC secured server hard-drive in order to further protect from unauthorized access and loss of research data.

Hard copies, including Parental consent forms will be stored separately in a locked drawer in a locked office.

**B. Will any of the following subject identifiers be obtained from the medical record and/or directly from the subject or their LAR and maintained (at any time) in association with the research data?** [See Educational Guide – Biomedical Research \(PedsIRB\)](#)

☐ **No**

☒ **Yes. Respond to the following:**

**1) Indicate the subject identifiers that will be recorded:**

☒ **Name**

☐ **Postal address information: street address, city, county, precinct, ZIP code**

☐ **All elements of dates (except year) related to an individual (e.g. birth, admission, discharge)**

☐ **Telephone numbers**

☐ **Fax numbers.**

☐ **Electronic mail addresses**

☐ **Social Security numbers**

☒ **Medical Record numbers**

☐ **Health plan beneficiary numbers**

☐ **Account numbers**

☐ **Certificate/license numbers**

☐ **Vehicle identifiers and serial numbers, including license plate numbers**

☐ **Device identifiers and serial numbers**

☐ **Web Universal Resource Locators (URLs)**

☐ **Internet Protocol (IP) address numbers**

☐ **Biometric identifiers, including finger and voice prints**

☐ **Full face photographic images [and any comparable images]**

☐ **Any other unique identifying number, characteristic, or code]**

**2) What is the justification for recording the specific identifiers listed above?**

[See Educational Guide – Biomedical Research \(PedsIRB\)](#)

The identifiers listed above will be maintained while the infant is hospitalized in the NICU. Data will be collected and entered into a database while the infants is hospitalized. After the infant is discharged, the name and medical record number will be deleted from the database and the data will be assigned a subject number. Blood samples that are sent to Creighton for analysis will be de-identified and sent with the subject number.

